## 6.8 Preparation and storage of inoculate

Following inclusion volunteers will be requested to leave a faecal sample. The faecal sample will be left at Danderyds hospital or Mälarsjukhuset, Eskilstuna.

The faeces will be homogenized, filtered and glycerol added before freezing. The faeces will be thawed prior to capsulation and a surfactant and vegetable oil added. Capsules will be filled with this inoculate.

## 6.9 Treatment

Participants will come to the Department of Infectious Diseases, Danderyds hospital or Mälarsjukhuset in Eskilstuna the day prior to treatment start to collect clindamycin and for a final briefing. All participants will be requested to take 300 mg clindamycin capsules morning, lunch and evening for seven days. This will be followed by a two and a half day washout period. On day three of the washout period participants will return to Hospital to take the first IMP or placebo dose supervised and to collect their remaining study capsules that are to be stored in a freezer at home. Participants will then be requested to take two study capsules twice daily for a total of five days.

An SMS text message will be sent twice daily to remind volunteers to take the clindamycin and study capsules. Patients and investigators will be blinded as to the content of the capsules. The code will be held by the manufacturers of the capsules that are not involved in the clinical part of the study.

## 6.10 Monitoring and follow up:

Upon inclusion clinical records form (appendix A) will be completed.

Stool habits and characteristics will be monitored daily from treatment start until day 28 and at 2 and 6 months using the structured questionnaire in appendix B. Questionnaires record stool frequency and consistency, general and gastrointestinal well-being via a standardized health score, rating of gastrointestinal symptoms and medication use. Overall and gastrointestinal-specific health scores will be reported on a scale of 1 to 10, with 1 being the lowest and 10 being “best possible health for you.”

Stool samples for sequencing will be taken at baseline and on days 10, 16 (+3 days if necessary), 28 and at 2 and 6 months.

**Table 1. Outline of study and sampling**

| Days |  | 1 | 1-7 | 8-10 | 10-15 | 16 | 28 | 2 months | 6 months |
| --- | --- | --- | --- | --- | --- | --- | --- | --- | --- |
| Phase | Inclusion | Start | Antibiotic | Washout | Treat | Follow up | | | |
| CRF A | + |  |  |  |  |  |  |  |  |
| *C.diff* screening | + |  |  |  |  |  |  |  |  |
| Faecal sample* | + | + |  | + |  | + | + | + | + |
| CRF B |  | + | + | + | + | + | + | + | + |
| Hospital visit | + | + |  | + |  | + |  |  |  |

*Prior to study start a faecal sample for autologous transplant will be donated.

## 6.11 Laboratory Procedures

### 6.11.1 Stool sampling for capsule preparation and sequencing:

A same day stool sample (minimum volume approximately 2 table spoons full) stored in a dedicated container will be delivered to Danderyds Hospital or Mälarsjukhuset as outlined in Table 1. The sample will then be transported to Reagensia AB, Solna and to SciLife Lab, Solna for capsule preparation and analyses of bacterial composition (microbiota).

### 6.11.2 Study of the intestinal microbiota:

Massive parallel sequencing will be performed. The patient will take a stool sample (approximate one spoon in dedicated device) immediately after defecation and introduce it into a transport medium for subsequent microbiota analyses in a sterile tube. Samples will be sent by ordinary mail (using standard shipping procedures) to the hospital laboratory and frozen upon arrival at minus 70 0C

Sequencing libraries for microbiota profiling will be prepared by amplifying the V3-V4 region of the 16S rRNA gene. After the initial amplification a second PCR will be performed to attach Illumina adapters as well as barcodes that allows for multiplexing. Samples will be sequenced using the Illumina MiSeq, whereafter primer sequences will trimmed away and the paired-end reads produced by the sequencing instrument will be merged using SeqPrep verson 1.1 (<https://github.com/jstjohn/SeqPrep>) with default parameters and thereafter processed with the QIIME 1.8.0 pipeline (Quantitative Insight Into Microbial Ecology). Using this pipeline, sequences will be clustered at 97% identity against the Greengenes reference database ([18](#_ENREF_18)).

## 6.12 Biobank

Stool samples and blood samples will be stored as part of the Karolinska Institutet biobank.

# 7. SAFETY AND ADVERSE EVENTS

## 7.1 Specification of safety parameters

Safety parameters; Adverse drug reactions and serious adverse drug reactions and changes in vital signs.

Any apparent side effects experienced by the subject will be assessed from the time the subject signs the informed consent and throughout the course of the entire study, and will be reported by study site personnel either as a Baseline Event or an AE (6.2). The study personnel will document any Baseline Events or AEs in the CRF, whether observed by the Investigator or reported by the subject. The safety of the different treatment arms will be assessed with regard to AEs, baseline medical conditions, and findings from the physical examination and laboratory tests.

Possible adverse events will be elicited using a modification of the Common Terminology Criteria for Adverse Events version 3.0. as used by Youngster et al ([13](#_ENREF_13), [19](#_ENREF_19)). Fever, gastrointestinal symptoms, headache, fatigue, and rash will be the principle symptoms evaluated (appendix B).

The AE reporting period is described in Section 6.2.

## 7.2 Adverse event

### 7.2.1 Definition

An AE in this study is defined as any untoward medical occurrence in a subject who has received investigational medicinal product (IMP). The occurrence does not necessarily need to have a causal relationship with the IMP. An AE can therefore be any unfavourable and unintended sign (including an abnormal laboratory finding), symptom, or disease temporally associated with the administration of IMP, whether or not causally related.

The occurrence of an AE may come to the attention of study personnel during study visits and interviews of a study recipient presenting for medical care, or upon review by a study monitor who is scrutinising relevant source data.

Clarifications:

Diagnostic and therapeutic non-invasive and invasive procedures, such as surgery, should not be reported as AEs. However, the medical condition for which the procedure was performed should be reported if it meets the definition of an AE. For example, an acute appendicitis that begins during the AE reporting period should be reported as “acute appendicitis” and the resulting appendectomy noticed under Comments. Pre-study conditions, which led to elective surgery during the time of the study, are not to be reported as AEs.

If an abnormal laboratory value or vital sign is associated with corresponding clinical signs and symptoms, the sign/symptom should be reported as the AE and the associated laboratory result or vital sign should be considered additional information that is to be collected in the CRF.

## 7.3 Serious adverse event

### 7.3.1 Definition

An SAE in this study is defined as any untoward medical occurrence that meets one of the following criteria:

- Results in death
- Is life threatening (the term “life threatening in the definition of “serious” refers to an event in which the subject was at risk of death and the time of the event; it does not refer to an event which hypothetically might have caused death if it was more severe)
- Requires inpatient hospitalization or prolongation of existing hospitalization
- Results in persistent or significant disability/incapacity
- Is an important medical event

## 7.4 Rating scales

The Investigator is to record all directly observed AEs and all AEs spontaneously reported by the subject in the subject’s records (source data) and in the CRFs using concise medical diagnostic terminology. All AEs must be graded for:

- seriousness
- intensity
- causality (possible relationship) to the IMP

The question asked will be “Have you had any health problems since your last evaluation?” If no AE has occurred during the period concerned, this should actively be noted in the CRF.

### 7.4.1 Intensity

The expression intensity of adverse events means the intensity of the event in the opinion of the subject. The intensity of each AE is to be graded by the Investigator.

### 7.4.2 Causality

The relationship between the IMP and each AE has to be classified by the Investigator using one of the following terms:

Unlikely: The onset of the AE and administration of the IMP are such that the medication is not likely to have any reasonable association with the AE.

Possible: It might be possible that the AE could have been caused by the IMP.

Probable: It is probable that the AE is caused by the IMP.

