# 1 BACKGROUND

*Clostridium difficile* is a toxin producing bacillus and an opportunistic pathogen that causes diarrhoea and colitis. *Clostridium difficile* infection (CDI) is a common and increasingly severe, primarily nosocomial infectious disease associated with a 2.5 fold increased 30 day mortality ([1](#_ENREF_1), [2](#_ENREF_2)). In the US there were an estimated 453 000 cases and 29 300 deaths in 2011 ([3](#_ENREF_3)). Swedish laboratories reported ~9575 episodes of CDI in Sweden in 2015 ([4](#_ENREF_4)). CDI usually occurs following antibiotic mediated destruction of the intestinal bacterial composition (microbiota) and can occur several weeks after antibiotic treatment. In line with this, the most pronounced disruption of the intestinal microbiota was during the 1^st^ month but changes lasted for at least 12 months in healthy volunteers taking clindamycin for 10 days ([5](#_ENREF_5)). Other risk factors for CDI include hospital admission, advancing age and severe underlying disease ([6](#_ENREF_6)).

A first episode of CDI is treated with metronidazole or vancomycin for 10 days. However, CDI recurs in up to 30% of patients after a first episode and in up to 60% after two or more recurrences ([7](#_ENREF_7), [8](#_ENREF_8)). The concept of treating CDI with additional antibiotics instead of reconstituting the gut flora has recently been challenged. Faecal microbiota transplantation and vancomycin treatment cured 81-94% and 23-31% of patients, respectively in a ground breaking randomised clinical trial in patients with recurrent CDI ([9](#_ENREF_9)). The effectiveness of inoculating microbiota for treatment of recurrent CDI has since been confirmed ([10-13](#_ENREF_10)). In line with this, we achieve approximately 90% treatment success when faecal microbiota transplantation, given as an enema, is used in routine clinical practice for treatment of recurrent CDI at Danderyds hospital (unpublished data). In essence faecal microbiota transplantation results in reconstitution of the normal intestinal microbiota by inoculation of a healthy individual’s microbiota into the diseased gut.

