# 3. Cost benefit assessment

The risk posed to participants are primarily allergic reactions to the antibiotic used (clindamycin) and antibiotic associated diarrhoeal disease, particularly CDI, caused by clindamycin. Clindamycin is well tolerated and rarely causes allergic reactions and the optimal treatment of CDI is inoculation with healthy intestinal microbiota which half the study participants will receive and all can do in case CDI develops. Moreover, study participants are screened for *C. difficle* prior to study entry so the risk of CDI is very low. Inoculation with intestinal microbiota has in repeated trials been shown to be well tolerated and our clinical experience is also that this treatment is well tolerated. Should anyone accidentally bite the capsule this will be disgusting but not hazardous to health. Theoretically a participant might vomit and the inhale the contents of the capsules. This is likely to cause a severe pneumonia. However, participants are healthy volunteers and the number of tablets taken at each time point is small. The risk of aspiration pneumonia is therefore exceedingly small. The potential benefit of this treatment is to develop a rapidly available treatment for CDI and for prevention of CDI, a disease that causes considerable morbidity and mortality and for which current treatment regimens are either suboptimal or very cumbersome. The benefits therefore considerably outweigh the potential risks.

#

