## 7.7 Sponsor’s reporting of serious adverse drug reactions and suspected unexpected serious adverse events

The Investigator and /or Bactavia or designee have to make a causality (relationship) assessment. The term SADR (Serious Adverse Drug Reaction) is to be used when the Investigator deems the SAE as possibly or probably related to the IMP. Serious Adverse Drug Reactions are to be reported annually to the MPA and the ethical committee.

If the event is not described before, e.g*.* in the IB, the event is a SUSAR (Suspected Unexpected Serious Adverse Event). Bactavia or designee has the obligation to submit SUSAR reports electronically to the Eudravigilance database within:

- 7 days if fatal or life-threatening (follow-up information within an additional 8 days)
- 15 days if non-fatal and non-life-threatening (follow-up information as soon as possible)

The following bodies are recipients of the reports, and procedures for such reports are familiar to investigator or designee:

- MPA
- European Medicines Agency (EMA)
- The study approving IEC

Bactavia has delegated the task of reporting SADR/SUSARs to the investigator, but has the ultimate responsibility for the fulfilment of these tasks. This delegation is enforced in a written delegation.

Bactavia also has the obligation to, once a year throughout the clinical study (or on request); submit a safety report to the MPA and the IEC taking into account all new available safety information received during the reporting period.

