## 7.8 Stopping rules

If an attending physician assesses that a patient is suffering from an adverse event induced by the IMP and requiring treatment, IMP treatment will be stopped for that patient. The outcome will be classified as an adverse event necessitating treatment stop. Should a study participant develop CDI this will be treated as per routine with metronidazole and in case of recurrence with autologous faecal transplant as per routine.

The data and safety monitoring board and the Swedish Medical Products Agency have the right to stop the study.

A study subject can terminate his/her participation in the study at any time without giving a reason why as outlined in patient information (appendix C). Should a subject wish to do so he/she will be treated in line with standard recommendations.

Study organisers can end a patient’s participation for safety reasons.

If a patient is excluded, already collected data will be used in subsequent analyses unless he/she objects.

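### Causality is graded against the study capsule alone, so a clindamycin reaction that starts after the first capsule cannot be recorded as one

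*Protocol*

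**What the plan says.** Section 7.4 lists what each adverse event must be graded for: seriousness, intensity and "causality (possible relationship) to the IMP". Section 7.4.2 repeats the last item, "The relationship between the IMP and each AE has to be classified by the Investigator using one of the following terms", and gives three terms: unlikely, possible and probable. The definition of Unlikely begins "The onset of the AE and administration of the IMP are such that the medication is not likely to have any reasonable association". It turns on when the event began relative to the IMP and does not mention another likely cause. No section asks for the relationship to clindamycin.

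The protocol has no formal definition of the IMP, but its usage is clear. In section 6.9 participants come back after the clindamycin washout to "take the first IMP or placebo dose supervised". Sections 7.5 and 7.6 start the reporting period at capsule administration and count six months from the end of IMP administration.

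Section 3 places the main risk elsewhere: "The risk posed to participants are primarily allergic reactions to the antibiotic used (clindamycin) and antibiotic associated diarrhoeal disease, particularly CDI, caused by clindamycin". Section 1 adds that CDI "can occur several weeks after antibiotic treatment". Section 7.1 puts gastrointestinal symptoms and rash among the main symptoms to be asked about.

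The causality judgement is then used. Section 7.1 names adverse drug reactions and serious adverse drug reactions as safety parameters. Section 7.7 applies the term SADR "when the Investigator deems the SAE as possibly or probably related to the IMP", and an event not described before becomes a SUSAR.

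**The concern.** Two products are given in close sequence, and the one that the protocol regards as riskier has no causality field. Suppose an investigator, blinded to capsule content, sees diarrhoea or a rash during the capsule course. Two kinds of record are possible. The event can be marked Unlikely, which is the right answer for the capsule if clindamycin was the cause, but the clindamycin link is then lost. Or it can be marked Possible or Probable, and it then counts as a capsule reaction. Because Unlikely is worded around timing, an event that falls during or soon after capsule intake fits it poorly, even when the investigator believes the antibiotic is the better explanation.

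At stake is how the capsule's own safety profile will read: the number of related events, the list of adverse drug reactions, and the class given to any serious case. With 12 participants per arm and no power calculation (11.1), single attributed cases will weigh heavily in that reading.

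**Working it through.** The protocol states no figure on this point, so there is none to reproduce. Three checks were made.

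**1. Timing.** Inputs: clindamycin on days 1 to 7 in both arms (6.1, Table 1); a washout of two and a half days, with the first capsule on day 10 (6.9, Table 1); capsules for five days, ending on day 14 or 15 depending on how the half days are counted (6.9, Table 1); primary window up to 21 days after the last capsule (5.1).

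- Window closes: 14 + 21 = day 35, or 15 + 21 = day 36.
- Window start relative to the last clindamycin day: 10 − 7 = 3 days.
- Window end relative to the last clindamycin day: 35 − 7 = 28 days, or 36 − 7 = 29 days.

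The whole primary window therefore lies 3 to 29 days after clindamycin, within the several weeks that section 1 gives for CDI. Take diarrhoea starting on day 12. It comes 12 − 7 = 5 days after the antibiotic and 12 − 10 = 2 days into the capsules. Timing alone cannot separate the two causes, and timing is all that the definition of Unlikely offers.

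**2. Size of the mislabelling (illustration with assumed rates).** Let p be the proportion of participants with a clindamycin event in the window, and q the proportion of those events graded possible or probable for the capsule. Assume that the capsule has no effect. In an arm of 12, the expected number with a capsule-related label is 12 × p × q, and the chance of at least one is 1 − (1 − pq)^12.

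| p | q | Expected of 12 | Chance of at least one |
| --- | --- | --- | --- |
| 10% | 25% | 12 × 0.025 = 0.3 | 26% |
| 10% | 100% | 12 × 0.10 = 1.2 | 72% |
| 30% | 50% | 12 × 0.15 = 1.8 | 86% |
| 50% | 25% | 12 × 0.125 = 1.5 | 80% |
| 50% | 100% | 12 × 0.50 = 6.0 | over 99% |

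Under blinding the same expectation applies to the 12 placebo participants. The range is wide because the documents give neither p nor q.

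**3. The between-arm comparison.** Section 11.3 compares proportions of adverse events between arms with a χ² or Fisher exact test and does not use the causality grade. For a two-sided Fisher test at 5% with 12 against 12, and the same background rate in both arms, the exact false-positive rate is:

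- 0.25% at a background rate of 10%
- 1.2% at 20%
- 1.7% at 30%
- 2.3% at 50%

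A shared clindamycin background does not push it above 5%.

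**The case against.** The strongest reply is that the design already protects the main question. Clindamycin goes to everyone, allocation is randomised and blinded, and 11.3 compares all events. If clindamycin reactions are called capsule-related equally often in both arms, the placebo arm shows it. This stands. A reader might infer that the primary safety comparison is biased, and the documents do not support that. What the arm comparison cannot do is correct the class of an individual serious case, or say how many labelled reactions belong to the antibiotic.

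Other stronger readings also fail:

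- **Capsules stopped because of the grade.** Section 7.8 acts when a physician judges that a participant is "suffering from an adverse event induced by the IMP and requiring treatment". That is a separate judgement, in stronger terms than Possible, and it is not tied to the 7.4.2 grade.
- **Clindamycin side effects fill the whole window.** The first-month statement in section 1 concerns microbiota disruption after a 10-day course in another study, not adverse reactions after seven days. The delay of several weeks is stated for CDI only, whose risk section 3 calls very low after screening. The same section calls allergic reactions rare.
- **Investigators will tend to mark Possible.** No document gives a rate. The wording makes Unlikely hard to justify, but how often that changes a grade is unknown.
- **Unblinding for a known antibiotic effect.** Under 7.7 and 6.6.1 this needs an event that is serious, at least possibly related and not previously described. Nothing indicates how often that would occur in 24 healthy volunteers.

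It can also be said that the case record forms in appendices A and B are not part of the text at hand and might hold an alternative-cause item. However, 7.4 itself lists what must be graded, and clindamycin is not on the list. The questionnaire item on medication use (6.10) records exposure, not relationship.

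**Conclusion.** The point holds for events that start after the first capsule. Sections 7.4 and 7.4.2 give no way to record a clindamycin reaction as one, and Unlikely is defined by timing that cannot separate products given about three days apart. Capsule-related counts, the adverse drug reaction parameter (7.1) and the SADR/SUSAR class (7.7) can therefore include background-drug effects in both arms. The size cannot be fixed from the protocol. The range of 0.3 to 6.0 of 12 rests wholly on assumed rates of 10–50% and 25–100%. The blinded comparison of all adverse events is unaffected, so this is a worthwhile, low-cost improvement and no more.

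It does not extend to reactions before the first capsule, where a different gap appears. Section 7.1 assesses events from consent, but 7.5 and 7.6 start reporting at capsule administration, and 7.2.1 defines an adverse event as occurring in someone who has received the IMP. Reactions during clindamycin dosing may thus not be graded at all.

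The conclusion assumes that IMP means the study capsule. Section 8.10 names betamethasone as the investigational product, which conflicts with the rest of the protocol and needs reconciling. No section makes clindamycin the IMP.

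**What to change.** - In 7.4 and 7.4.2, grade each adverse event twice, blinded: once against clindamycin and once against the study capsule, whether active or placebo.
- Let Unlikely, or an added level of not related, reflect a more plausible alternative cause and not timing alone.
- Report related events by product and by arm.
- In 7.7, state that serious reactions attributed to clindamycin are classified against the clindamycin reference information.
- Reconcile the start of recording in 7.5 and 7.6, and the definition in 7.2.1, with 7.1, so that reactions during clindamycin dosing are also graded.
- Leave the stopping provision in 7.8 as it is.

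The cost is one more field on the case record form, a few sentences of protocol text and slightly more investigator work per event. An investigator in doubt may still mark Possible for both products. The change does not remove that uncertainty, but it makes it visible in the data.
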